## Abstract

**Background:**

The German health care system maintains a strict division between inpatient and outpatient care, posing challenges for the continuity of care. Discharge management facilitates the transition from inpatient to outpatient settings. For psychiatric patients, sociotherapy is one transitional intervention that can be prescribed to inpatients at discharge and then provided in the outpatient setting. As a form of case management, it aims to motivate patients, coordinate care among providers, and ultimately reduce psychiatric hospital readmissions. However, the effectiveness of sociotherapy remains unclear due to a lack of randomized trials. This protocol describes an observational study investigating the causal impact of sociotherapy on psychiatric readmission rates.

**Methods:**

We will use claims data from the largest statutory health insurance provider in Germany to evaluate the effect of sociotherapy as a discharge management measure on 30-day readmissions among patients who received psychiatric inpatient treatment. To reduce potential bias in this observational study we will use the target trial emulation framework. Quasi-randomization will be achieved through Propensity Score based methods, controlling for characteristics of the index event, patients' medical history, and relevant sociodemographic factors. Intention to treat and per protocol effects will be estimated with logistic regression models. Furthermore, we will analyze 365-day readmission rates, time to first psychiatric hospitalization within 365 days, total number of psychiatric hospitalizations within 365 days, and cumulative number of days in hospital due to psychiatric admissions within 365 days as secondary outcomes.

**Conclusion:**

Our study will evaluate the effectiveness of sociotherapy as a transitional intervention following psychiatric hospitalization. By employing the Target Trial Emulation framework, we aim to generate robust, real-world evidence that can guide both clinical practice and policy-making, ultimately contributing to improved continuity of care for psychiatric patients.

**Trial Registration:**

Trial registration: DRKS, ISRCTNDRKS00035987. Registration on 17 February 2025—Retrospectively registered, https://drks.de/register/de/trial/DRKS00035987

**Supplementary Information:**

The online version contains supplementary material available at 10.1186/s12913-025-13137-2.

## Contributions to the literature

The present study addresses the critical evidence gap on the effectiveness of sociotherapy, an transitional intervention currently embedded in German legislation and clinical practice.The study protocol outlines a Target Trial Emulation (TTE), which is a framework to evaluate causal effects based on observational real-world data. By applying this rigorous approach, we aim to generate robust evidence regarding the effectiveness of sociotherapy as a discharge management (DM) measure.When applicable, the findings will aid practitioners and policymakers in guiding clinical decisions and shaping policy, fostering evidence-based decision-making.

## Background

Historically, the German health care system was characterized by a strict division between inpatient and outpatient care, leading to a number of challenges in ensuring the continuity of care for patients following hospitalization [1]. To address these challenges, the German Social Code was amended in 2017 to establish mandatory standards for hospital discharge management (DM) with the aim of improving the transition from inpatient to outpatient care. Under this reform, hospitals are now authorized to prescribe medication, remedies and aids, as well as special services including sociotherapy, home care, specialized outpatient palliative care, digital health applications and transportation services. Hospitals may also certify the incapacity to work if needed and are obliged to provide a discharge document including a medication plan. Since this policy reform was introducedto facilitate the transition from inpatient to outpatient care, the duration of any measures is limited to seven days after discharge. If necessary, the measures may be continued by outpatient providers. Hospitals are mandated to initiate interprofessional discharge planning as early as possible to enhance continuity of care. This paradigm shift in the implementation of DM was enacted through a framework agreement between the National Association of Statutory Health Insurance Funds (GKV), the National Association of Statutory Health Insurance Physicians (KBV) and the German Hospital Federation (DKG) [2].

The main focus of the present paper is sociotherapy, an intervention that aims to support individuals with severe mental health disorders (i.e., schizophrenia, bipolar disorder or chronic depression). This patient-centered approach was included as a key measure in the 2017 German health care reform to improve DM and is especially relevant for psychiatric patients. As a form of structured case management, sociotherapy aims to improve coordination among healthcare providers involved in a patient’s treatment and support patients in utilizing needed healthcare services. Further goals are to foster social participation through the engagement of the patient’s social network and to offer crisis intervention if needed. In line with the Recovery Framework in mental health, the focus of sociotherapy does not lie on reducing psychiatric symptoms but rather emphasizes practical, social and daily life skills [3, 4]. Among other measures, sociotherapy ultimately aims to reduce or shorten psychiatric hospital stays [5]. Sociotherapy is typically provided by trained mental health professionals, including social workers, psychiatric nurses, and specialized therapists. Sociotherapy can be prescribed as a transitional DM measure, ideally starting immediately after discharge. To this end, an initial prescription can be issued by the hospital that lasts up to seven days, after which continued treatment requires a prescription from a licensed outpatient health care professional. In total, up to 120 sociotherapy sessions can be prescribed over a three-year period [6].

Sociotherapy as implemented in Germany shares similarities with various forms of case management found in other countries, particularly in the context of mental health care. For example, models such as Case Management (CS), Intensive Case Management, Critical Time Intervention (CTI), or Care Programme Approach (CPA) in the United Kingdom also emphasize coordinated, patient-centered care aimed at supporting individuals with severe mental illnesses [7]. Commonalities include involvement of the patient’s social network, and a focus on improving access to necessary health and social services. However, there are notable differences: the German sociotherapy framework is embedded in statutory health insurance, whereas similar programs elsewhere might operate under different funding mechanisms, timeframes or case load.

Although sociotherapy is covered by German health insurance funds for patients with severe mental health disorders, its effectiveness remains largely unexamined. This study protocol outlines a Target Trial Emulation (TTE) designed to evaluate the impact of sociotherapy as a transitional intervention on the 30-day psychiatric readmission rate. The TTE framework is particularly well suited for this purpose as it bridges the gap between randomized controlled trials (RCTs) and observational research [8, 9]. Conducting an RCT for an intervention already established by law would be challenging due to financial and logistical constraints. By systematically addressing potential biases, the TTE allows us to mimic a RCT using real-world data and gain robust evidence regarding the role of sociotherapy in provision of care in psychiatric patients.

### Design

The aim of this study protocol is to describe the emulation of a target trial designed to estimate the causal effect of sociotherapy as a DM measure using observational data from insurance claims records. Following the principles of TTE, we define the hypothetical RCT that we seek to emulate [8, 9]. Based on the primary outcome of interest (30-day readmissions), the sample size for the target trial was calculated. We then provide a detailed description of the TTE using observational data, covering key aspects such as included variables, eligibility criteria, treatment strategies, assignment procedure, follow-up period and outcomes definitions (for a comparison between hypothetical target trial and emulation see Table 1). And finally, we outline the statistical analysis strategy for the TTE.

**Table 1 Tab1:** Target Trial Emulation

	**TARGET TRIAL**	**E2-PSY TRIAL EMULATION**
Eligibily Critera	Inclusion criteria • Adults aged 18 years or over • Patients with a psychiatric treatment in an inpatient, semi-inpatient or inpatient equivalent setting Exclusion criteria • Previous sociotherapy	Inclusion criteria • • Adults aged 18 years or over • Patients with a psychiatric treatment in an inpatient, semi-inpatient or inpatient equivalent setting (PEPP classification PO, PP, PA, TP, or QA) Exclusion criteria • Previous sociotherapy within 365 days before the last day of the index event • No continuous health insurance throughout the study period • Personnal of the insurance provider supplying the data • Existing data protection notice • Existing objection to use of healthcare records for research purposes
Treatment Strategies	Intervention group • Prescription of sociotherapy as acomponents of discharge management (last day of the index event) Control group • No prescription of sociotherapy as a componentof discharge management (last day of the index event)	Intervention group • Prescription of sociotherapy as a components of discharge management (last day of the index event) Control group • No prescription of sociotherapy as a component of discharge management (last day of the index event)
Assignment procedures	Participants will be randomly assigned to either treatment armon the last day of the index event. Patients will be aware of the treatment armthey have been assigned to	Quasi-randomization will be archived through a propensity score-based method, either propensity score matching or inverse probability weighting
Follow-Up Period	Starts at randomization and ends 30 days/365 days after discharge of the index event, death, or loss to follow-up	Starts at the last day of the index event and ends 30 days/365 days after discharge of the index event, death, or loss to follow-up
Outcome	Primary outcome • Readmission to hospital for psychiatric treatment within 30 days after discharge Secondary outcomes • Readmission to hospital for psychiatric treatment within 365 days after discharge • Time to first psychiatric rehospitalization • Total number of rehospitalizations within 365 days after discharge • Cumulative number of days spent in the hospital due to psychiatric admissions during 365 days after discharge	Primary outcome • Readmission to hospital for psychiatric treatment within 30 days after discharge Secondary outcomes • Readmission to hospital for psychiatric treatment within 365 days after discharge • Time to first psychiatric rehospitalization • Total number of rehospitalizations within 365 days after discharge • Cumulative number of days spent in the hospital due to psychiatric admissions during 365 days after discharge
Causal Contrasts Of Interest	• Intention-To-Treat (ITT): The ITT evaluates the average treatment effect among the treated (ATT), regardless of whether the patients adhered to the treatment • Per-Protocol (PPA): The PPA evaluates the average treatment effect among the treated (ATT), accounting for the non-adherence to the sociotherapy treatment in the intervention group, and usage of sociotherapy in the control group due to prescriptions of sociotherapy unrelated to the assignment procedure	• Intention-To-Treat (ITT): The ITT evaluates the average treatment effect among the treated (ATT), regardless of whether the patients adhered to the treatment • Per-Protocol (PPA): The PPA evaluates the average treatment effect among the treated (ATT), accounting for the non-adherence to the sociotherapy treatment in the intervention group, and usage of sociotherapy in the control group due to prescriptions of sociotherapy unrelated to the assignment procedure
Analysis Plan	• Logistic regression models for the primary outcome readmission to hospital for psychiatric treatment within 30 days after discharge and the secondary outcome readmission to hospital for psychiatric treatment within 365 days after discharge • Cumulative incidence curves and a log-rank test, as well as Cox-regression models for the outcome time to first psychiatric treatment • Poisson Regression (or negative binominal regression) for the outcomes total number of hospitalizations within 365 days after discharge and cumulative number of days spent in the hospital due to psychiatric admissions during 365 days after discharge	• Logistic regression models for the primary outcome readmission to hospital for psychiatric treatment within 30 days after discharge and the secondary outcome readmission to hospital for psychiatric treatment within 365 days after discharge • Cumulative incidence curves and a log-rank test, as well as Cox-regression models for the outcome time to first psychiatric treatment • Poisson Regression (or negative binominal regression) for the outcomes total number of hospitalizations within 365 days after discharge and cumulative number of days spent in the hospital due to psychiatric admissions during 365 days after discharge

### Sample size calculation

The required sample size for thetarget trial was determined based on the primary outcome of interest: the 30-day hospital readmission rate. To achieve sufficient statistical power (80%) to detect a minimal clinically relevant difference in the 30-day readmission rates (effect size = 0.3) between participants receiving sociotherapy and those receiving standard care, we conducted a priori power calculations (Appendix 1). Since the required sample size depends not only on the effect size but also on the outcome rate in the non-exposed group– a figure currently unknown– we calculated a range of sample sizes across plausible outcome rates [10]. Assumingan effect size of 0.3, the necessary sample size is N = 449 when the baseline readmission rate is 10%, and decreases to N = 329 when the baseline rate increases to 20%. If the required sample size based on the outcome rate in the non-exposed group (see Assignment Procedure) is not reached in our dataset, the TTE will be discontinued, and the journal will be notified. A detailed explanation outlining the reasons for the termination will be provided to ensure transparency and maintain the integrity of the study’s reporting. Exploratory analysis may be conducted.

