## Discussion

By employing the TTE framework, we adopt a systematic approach that minimizes the risk of bias when analyzing real-world data, thereby enhancing the reliability and validity of our findings. If feasible, our study will be among the first to provide robust evidence on the effectiveness of sociotherapy for reducing readmission rates among psychiatric inpatients. However, the insurance claims data used in this study provide limited and potentially less reliable information on key social determinants, such as social support, family or employment status. As a result, we are unable to account for these potential confounders, which may influence the primary and secondary outcomes. Furthermore, the reduction in psychiatric readmissions or the shortening of psychiatric hospital stays are not the only potential benefits of sociotherapy. Our study does not evaluate the impact of sociotherapy impact on the utilization of outpatient healthcare services and better coordination between healthcare providers, nor does it consider broader outcomes such as patient motivation, social participation, or the engagement of the patient’s social network, all of which are key goals of sociotherapy.

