## Conclusion

In conclusion, our study aims to provide robust evidence regarding the effectiveness of sociotherapy prescriptions as a DM component on psychiatric readmissions. By employing the TTE framework, we aim to minimize bias and enhance the reliability of our findings which are derived from real-world data. The study addresses a critical lack of evidence for a treatment which is codified in German law and covered by German health insurances. If sociotherapy proves to be effective on the reduction of psychiatric readmissions, the findings could support its broader implementation and integration into routine care. Conversely, if no significant effect is observed, the results could spark a renewed discussion about the treatment’s role and barriers—ranging from exploring other potential beneficial outcomes, such as improved social participation and patient engagement, exploring potential barriers of implementation especially in regard to a fast provision after hospital discharge versus long, bureaucratic processes, to reconsidering its inclusion in health insurance coverage.

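### The printed sample sizes of 449 and 329 reproduce only as per-group numbers for an increase in readmissions; for the reduction the study aims at, the same inputs need 609 and 400 per group at 1:1

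*Protocol article*

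**What the plan says.** The Sample size calculation section of the protocol article gives the purpose: "To achieve sufficient statistical power (80%) to detect a minimal clinically relevant difference in the 30-day readmission rates". The effect is described only as a "difference in the 30-day readmission rates (effect size = 0.3) between participants receiving sociotherapy and those receiving standard care". The results are that "the necessary sample size is N = 449 when the baseline readmission rate is 10%, and decreases to N = 329" when the baseline rate is 20%. For the details the section says "we conducted a priori power calculations (Appendix 1").

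The figures also act as a gate. The relevant sentence begins "If the required sample size based on the outcome rate in the non-exposed group" and goes on to say that, if this number is not reached in the dataset, the emulation is discontinued and the journal informed.

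The intended direction is clear elsewhere. The Abstract and Background name fewer or shorter psychiatric stays as an aim of sociotherapy. The Discussion speaks of the "effectiveness of sociotherapy for reducing readmission rates among psychiatric inpatients". The Conclusion considers what follows "If sociotherapy proves to be effective on the reduction of psychiatric readmissions", and says that a result without a significant effect could lead, among other things, to its insurance coverage being reconsidered.

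**The concern.** For a binary outcome well below 50%, an upward and a downward shift of the same standardised size do not need the same number of patients. The downward shift is the smaller absolute difference, and the smaller difference costs more patients even though its variance is also lower. A sample size worked out for an increase is therefore too small for the mirrored reduction, even when the test is two-sided.

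If 449 and 329 were obtained for an increase, they do not deliver 80% power for the effect of interest at equal group sizes. A planning figure of this kind often has little consequence in a claims-data study, where the sample is whatever the database holds. Here it decides whether the emulation goes ahead, so a threshold set too low lets an underpowered comparison pass as adequate. The authors themselves name a policy consequence of a null result.

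The bare N adds a second difficulty: a reader would naturally take it as the total.

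**Working it through.** **Inputs from the article.** Power 80%; effect size 0.3; baseline rates p0 = 10% and 20%; printed N = 449 and 329.

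**Inputs assumed, because the article does not state them.** Two-sided alpha 5% (z = 1.960; z for 80% power = 0.842); 1:1 allocation; 0.3 as a standardised difference (Cohen's d) on the probit scale; pooled-variance two-proportion formula without continuity correction; no dropout.

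**Formulas.** Exposed rate: p1 = Φ(Φ⁻¹(p0) ± 0.3). With p̄ = (p0 + p1)/2,

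n per group = [1.960·√(2p̄(1−p̄)) + 0.842·√(p0(1−p0) + p1(1−p1))]² / (p1 − p0)²

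**Step 1: reproduce the printed figures (shift +0.3, more readmissions).**
- p0 = 0.10: p1 = Φ(−1.2816 + 0.3) = 0.1632. n = [1.960 × 0.4781 + 0.842 × 0.4760]² / 0.0632² = 448.5, so 449 per group.
- p0 = 0.20: p1 = Φ(−0.8416 + 0.3) = 0.2940. n = [1.960 × 0.6099 + 0.842 × 0.6063]² / 0.0940² = 329.0, so 329 per group.

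Both printed numbers are matched to the patient by one set of inputs.

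**Step 2: look for a reduction that gives the same figures.** The readings tried were the probit and logistic conversions of d, d × 1.65, log odds ratio 0.3, odds ratios 0.3, 0.7 and 1/1.3, risk ratios 0.3 and 0.7, Cohen's h = 0.3, and the reciprocal of the odds ratios implied by Step 1. Each was run with alpha from 1% to 10%, one- and two-sided, power 80% and 90%, with and without continuity correction, at allocation ratios from 1:4 to 10:1, per arm and in total. None gives both 449 and 329.

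**Step 3: the mirrored reduction (shift −0.3, otherwise as in Step 1).**
- p0 = 0.10: p1 = 0.0569. n = [1.960 × 0.3802 + 0.842 × 0.3790]² / 0.0431² = 609 per group, 1,218 in total. That is 160 more per group than printed (609/449 = 1.36).
- p0 = 0.20: p1 = 0.1268. n = [1.960 × 0.5229 + 0.842 × 0.5203]² / 0.0732² = 399.4, so 400 per group, 800 in total. That is 71 more per group (400/329 = 1.22).

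The requirement depends somewhat on how the mirror image is defined. The logistic conversion of d (odds ratio 0.58) needs 745 and 399 per group. The reciprocals of the odds ratios implied by Step 1 (0.57 and 0.60) need 704 and 447. All exceed the printed figures.

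**Step 4: power for the probit-scale reduction at the printed sizes.** Power = Φ{[|p0 − p1| − 1.960·√(2p̄(1−p̄)/n)] / √([p0(1−p0) + p1(1−p1)]/n)}.
- 449 per group: (0.04312 − 1.960 × 0.01794)/0.01789 = 0.445, power 67% (exact enumeration 67.6%).
- 329 per group: (0.07319 − 1.960 × 0.02883)/0.02869 = 0.582, power 72% (exact enumeration 72.3%).
- N as a total, split equally: 40% and 43%. Even the increase would then have only about 51%.

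**Step 5: more controls per treated patient.** Same reductions, printed N taken as the number treated, unadjusted, with no allowance for precision lost to weighting:

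| Treated : control | 449 treated, 10% to 5.7% | 329 treated, 20% to 12.7% |
|---|---|---|
| 1:1 | 67% | 72% |
| 1:2 | 78% | 83% |
| 1:3 | 82% | 87% |
| 1:4 | 85% | 89% |

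**The case against.** The strongest reply is that the inputs are inferred. The article gives no scale, direction, alpha, sidedness or allocation, and Appendix 1 may declare them. The text speaks only of a difference, and the analysis section of an association; no formal directional hypothesis is stated. This stands as a limit on certainty. But two separate figures are matched exactly by one ordinary set of inputs, no reduction tried matches both, and the article is explicit that the benefit sought is fewer readmissions. An appendix that labels N as per group would settle the label and leave the direction unresolved.

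The second reply also has force. The Assignment procedures section leaves open matching or weighting and fixes no matching ratio. Claims data from an insurer with about 15.3% of the market could supply several controls per treated patient, although the article gives no counts. With three controls each, 449 or 329 treated patients would exceed 80% power for the reduction. A reader might infer that the emulation is bound to be underpowered; the documents do not support that, because the shortfall for a given number of treated patients depends on 1:1 allocation.

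Third, the shortfall at 1:1 is moderate. With 449 per group, 80% power is reached for a fall from 10% to 5.1% instead of 5.7%; with 329, for a fall from 20% to 12.0% instead of 12.7%.

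A reader might also infer that power is only about 40%. That requires the unlabelled N to be applied as a total, which the article does not say; the reproduction shows that the figures were calculated per group. Nor does the match mean that the authors expect harm. A positive sign entered by default in a conversion would give the same result.

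**Conclusion.** The point holds as a mismatch between the printed sample sizes and the study's aim. The arithmetic behind 449 and 329 is sound for an increase in readmissions, per group. For the reduction, on the same inputs and at 1:1, the requirement is 609 and 400 per group (36% and 22% more), and the printed sizes give 67% and 72% power instead of 80%. The drop to about 40% and 43% is a conditional worst case that follows only if N is used as a total.

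Confidence is high in the reproduction. It is lower for the power actually lost in the emulation, which depends on the unstated allocation, on matching or weighting, and on an adjusted logistic model that the unadjusted two-proportion formula only approximates. The conclusion also rests on reading 0.3 as a probit-scale shift with two-sided 5%, which the unseen Appendix 1 could confirm or contradict. Because the figure is a discontinuation threshold, it should be corrected before it is applied.

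**What to change.** In the Sample size calculation section and Appendix 1, state the scale and direction of 0.3, the absolute risks it implies, alpha and sidedness, the allocation ratio, and that the figures are per group. Then do one of the following:

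- Recompute the discontinuation threshold for a reduction: 609 per group (1,218 in total) for 10.0% to 5.7% and 400 per group (800 in total) for 20.0% to 12.7% at 1:1, or the corresponding number of treated patients at the planned matching ratio.
- Keep 449 and 329, label them per group, and state the power for a reduction as 67% and 72% at 1:1.

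The cost is one rewritten paragraph and a revised appendix. The stated figures become less favourable, and under the first option the threshold is harder to reach. No new data are needed.

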### Assignment procedures

To address potential confounding in the observational data we estimate propensity scores based on the probability of receiving sociotherapy. These scores will be calculated using logistic regression controlling for key characteristics of the index event, other prescribed DM measures, medical history and sociodemographic characteristics (for a detailed description see Table 2). Afterwards the propensity scores will be applied by either propensity score matching (PSM) or inverse probability weighting (IPW) depending on the distribution of the scores. Balance diagnostics such as standardized mean differences will be conducted and all steps of the procedure including the applied methods will be reported.

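### The rule for discontinuing the emulation rests on a sample size for a randomised trial, so it does not track the power of the matched or weighted analysis

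*Protocol article*

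**What the plan says.** All statements are in the protocol article.

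- **Sample size calculation.** The size belongs to the hypothetical trial: "The required sample size for thetarget trial was determined based on the primary outcome of interest". The target is a "minimal clinically relevant difference in the 30-day readmission rates (effect size = 0.3") with 80% power. The article states that "the necessary sample size is N = 449 when the baseline readmission rate is 10"% and that it "decreases to N = 329 when the baseline rate increases to 20"%. Details are referred to an appendix: "we conducted a priori power calculations (Appendix 1").
- **Same section, stop rule.** If the size required for the observed control-group rate "is not reached in our dataset, the TTE will be discontinued, and the journal will be notified". A detailed explanation will be given, and exploratory analysis remains allowed.
- **Assignment procedures.** The emulation will use "propensity score matching (PSM) or inverse probability weighting (IPW) depending on the distribution of the scores". No matching ratio is given. The stop rule points to this section, but the section does not say which patients count towards N.
- **Table 1 and Outcomes.** The estimand is the average effect among the treated.
- **Data.** The claims cover 2021 to 2024. The abstract dates registration to 17 February 2025.

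**The concern.** The number that decides whether the planned analysis goes ahead was derived for a different design. In a randomised trial with two equal arms, one N fixes the power. In a matched or weighted analysis of claims data it does not. Where controls far outnumber treated patients, precision depends mainly on how many were treated, how many controls each is matched to, and how much information the weights cost. The rule refers to none of these.

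This goes beyond detail that an article may leave to a fuller document. The rule is binding as written and can cancel the pre-specified primary analysis. What it allows in its place is an exploratory analysis of the same data, without the pre-specified plan that gives a target trial emulation its credibility.

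**Working it through.** **Inputs.** From the article: power 80%, effect size 0.3, baseline rates 10% and 20%, N = 449 and 329. Assumed, because the article does not state them and Appendix 1 is not shown: two-sided 5% test, 0.3 as a shift on the normal-deviate scale, equal arms, no continuity correction.

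**Step 1: reproduce the stated figures.** With p0 the baseline rate, p1 = Φ(Φ⁻¹(p0) + 0.3), d = |p1 − p0| and m the mean of p0 and p1:

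n per arm = [1.96·√(2m(1−m)) + 0.8416·√(p0(1−p0) + p1(1−p1))]² / d²

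- 10%: Φ(−1.2816 + 0.3) = 16.32%, d = 0.0632, n = (0.9370 + 0.4006)² / 0.0632² = 448.5, so 449.
- 20%: Φ(−0.8416 + 0.3) = 29.40%, d = 0.0940, n = (1.1954 + 0.5103)² / 0.0940² = 328.98, so 329.

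Both match exactly, as numbers per arm (898 and 658 in total) and for an increase in readmissions. A fall of the same size on that scale (10% to 5.69%, 20% to 12.68%) would need 609 and 400 per arm. Other readings of 0.3 that were tried (Cohen's h, risk ratios, odds ratios) did not give the pair, either per arm or as totals. Because the intended direction is a reduction, the power figures below cover both directions.

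**Step 2: power of an emulation with unequal groups.** Before any weighting loss, power = Φ(d/SE − 1.96), with SE = √(p1(1−p1)/n_treated + p0(1−p0)/n_control).

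| Baseline | Treated / controls | Direction | d | SE | d/SE | Power |
|---|---|---|---|---|---|---|
| 10% | 300 / 3,000 | increase | 0.0632 | 0.0220 | 2.87 | 82% |
| 10% | 300 / 3,000 | reduction | 0.0431 | 0.0145 | 2.98 | 85% |
| 20% | 250 / 2,500 | increase | 0.0940 | 0.0299 | 3.14 | 88% |
| 20% | 250 / 2,500 | reduction | 0.0732 | 0.0225 | 3.25 | 90% |
| 10% | 50 / 20,000 | increase | 0.0632 | 0.0523 | 1.21 | 23% |
| 10% | 50 / 20,000 | reduction | 0.0431 | 0.0328 | 1.31 | 26% |
| 20% | 50 / 20,000 | increase | 0.0940 | 0.0645 | 1.46 | 31% |
| 20% | 50 / 20,000 | reduction | 0.0732 | 0.0471 | 1.55 | 34% |

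The pool of 20,000 controls is an assumption.

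**Step 3: apply the rule under each reading.**

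- *N per arm.* The first four rows have fewer treated patients than 449 or 329, so they are stopped despite power above 80%.
- *N as a total of all eligible patients.* The last four rows have 20,050 patients, so they pass with power far below 80%.

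**Step 4: sensitivity to the variance formula.** With unequal groups the choice matters. Using the pooled variance under the null, as in step 1, power for 300 / 3,000 becomes 89% (increase) or 71% (reduction). For 250 / 2,500 it becomes 92% or 83%. For 50 / 20,000 it becomes 35% or 11% at a 10% baseline, and 40% or 21% at 20%. The conclusion remains. With the pooled formula, the treated patients needed for 80% power are:

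| Controls per treated | 10%, increase | 10%, reduction | 20%, increase | 20%, reduction |
|---|---|---|---|---|
| 1 | 449 | 609 | 329 | 400 |
| 2 | 327 | 472 | 243 | 307 |
| 5 | 253 | 387 | 190 | 250 |
| 10 | 228 | 359 | 172 | 231 |

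From five controls upwards, every entry lies below the corresponding 449 or 329.

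**The case against.** A feasibility gate announced in advance is defensible. This one depends on the control-group rate and not on the treatment effect, it commits the authors to notify the journal and explain, and it labels later work as exploratory. The discussion also says openly that the study may not prove feasible. All of that stands, and nothing here faults having a gate. But openness about a gate does not help if it measures the wrong quantity.

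Three stronger readings are tempting and are not supported.

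- *N is a total, and the rule both discards good studies and passes poor ones.* The article never calls N a total, and the figures reproduce per arm. On a total reading no well-powered study is discarded: with 448 or 328 patients in all, the best split gives only 51.1% or 50.7% power for the reproduced effect.
- *The rule lets weak 1:1 studies run, because 449 or 329 per arm gives only 67% or 72% power.* Those figures arise from reversing the effect to a reduction. For the effect that reproduces N, the same samples have 80%. Any problem of direction lies in the sample size calculation and is separate from the stop rule.
- *Weighting passes the rule automatically.* That holds only if every eligible patient counts. The article does not say so, and its intention-to-treat population is defined by the matching procedure.

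It would also go too far to say that stopping has no benefit. The documents are silent on cost.

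**Conclusion.** The point holds, as a cheap improvement. The stop rule applies a target-trial N to a matched or weighted analysis without saying whether N is per arm or total, or whether eligible, treated, matched or weighted patients count. It therefore does not track the power it is meant to protect.

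The likelier reading is per arm, and there the harm is a needless stop: 300 treated at a 10% baseline (82–85% power) or 250 at 20% (88–90%), with ten controls each, fall short of 449 and 329. If N is instead a total of eligible patients, the harm is leniency: 50 treated patients pass with 23–26% or 31–34% power. Only one of these can apply.

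The sizes rest on a two-sided 5% test, the normal-deviate reading of 0.3, the unpooled variance, the assumed control numbers, and no loss from weighting or gain from covariate adjustment. With the pooled variance and a reduction at the 10% baseline, 300 treated would be short of 80% power and about 359 would be needed, still below 449. The article does not give the number of treated patients in the data, so whether the rule would actually bite is unknown.

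**What to change.** 1. State N as per arm, with the alpha, sidedness and allocation behind it, and say which patients count towards it.
2. Base any feasibility gate on the number of treated patients, or on the effective sample size after matching or weighting, at the ratio actually used.
3. Let the gate decide only how the result is labelled. Run the pre-specified intention-to-treat analysis in any case, and report the number treated, the effective sample size and the effect estimate with its 95% confidence interval, marked as imprecise if wide. This replaces the unplanned exploratory analysis.

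The cost is a change of wording. The downside is that a result with a wide interval may have to be published.
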